Given the negative feedback mechanism of homeostatic plasticity, we can propose a priming-test preconditioning TMS tool that is more effective than the current stimulation alone. Initially, subjects will receive inhibitory priming to trigger their homeostasis response, followed by an excitatory test. As a result of the preceding inhibitory treatment, the neural network near the subject’s target area will more readily generate an excitatory response, leading to a more significant neural network activity during the excitatory test compared to the excitatory stimulus alone. Homeostatic plasticity plays a critical role in maintaining neural stability; thus, its impairment could limit the efficacy of NIN interventions. Research on myasthenia gravis (18), dystonia (19–21), Parkinson’s disease (22), Alzheimer’s disease (23), depression (24) and other psychiatric disorders (25) have highlighted deficiencies in homeostatic plasticity among patients, raising concerns about its preservation in DoC patients.

Therefore, prior to administering the combined stimulation to DoC patients, it is crucial to investigate the preservation of homeostatic plasticity in these individuals. This study is guided by two hypotheses: firstly, that DoC patients exhibit impaired homeostatic plasticity, with the degree of impairment correlated with their level of consciousness; and secondly, that patients who retain homeostatic plasticity may have a more favorable prognosis. To explore the retention of homeostatic plasticity in DoC patients, this study will employ two NIN technologies, tDCS and TMS, as assessment tools.

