### Participants

2.2

This study will include 15 patients with MCS, 15 patients with UWS, and 15 healthy subjects sourced from various hospitals. Before enrollment, each DoC patient will undergo five assessments using the Coma Recovery Scale-Revised (CRS-R) over a 10-day period conducted by assessment experts. The best result from the five assessments will be considered as the patient’s current level of consciousness, and assessment experts will assess if the patient meets the inclusion criteria during the evaluation process.

The criteria for inclusion and exclusion are outlined in Table 1.

**Table 1 tab1:** Inclusion and exclusion criteria.

Inclusion criteria	Exclusion criteria
Diagnosed in DoC with 5 times CRS-R assessments;	Active seizures or a history of mental illness;
Disease onset more than 28 day;	Metal implants in the skull;
Intact skin and anatomical structure;	Lack of motor evoked potential from right first dorsal interosseous muscle;
Right-handed as per Edinburgh Handedness Inventory;	Unstable vital signs;
Stable central nervous system drug therapy for 1 week before enrollment.	Use sedatives, sodium or calcium channel blockers.

DoC, disorders of consciousness; CRS-R, Coma Recovery Scale-Revised.

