### Procedures

2.4

The study process will begin as early as 28 days after the patient’s injury, and the entire experimental process will be finished within 10 days. After informing the patient’s legal representative about the experimental content and potential adverse reactions, written informed consent will be obtained from them. They will be advised that they can choose to exit the study at any time without the requirement for providing a reason. After informing the healthy subjects of the experimental content and potential adverse reactions, they will sign the informed consent form.

Before the trial, DoC patients will have the option to undergo a functional magnetic resonance imaging (fMRI) scan, and they can choose to decline. Over a period of 10 days, five CRS-R assessments, and an fMRI scan will be completed. The study protocol is a repeated-measures crossover design. According to different tDCS priming protocols (anode, cathode, sham), the trial will be divided into three distinct sessions. Each session will involve 10 min of tDCS priming followed by 192 s of TMS test, with both transcranial stimulations specifically targeted toward the left M1. We will measure the motor evoked potential (MEP) amplitude at four time points: baseline (PRE), after tDCS (INTER), and at 5 and 15 min following TMS (POST-1, POST-2). CRS-R data will be collected at baseline (PRE) and 20 min after TMS (POST-3). Upon enrollment, participants will receive a serial number based on their order of enrollment, with each serial number corresponding to a randomly generated session order. Subjects will then undergo three sessions following the designated session order, with a two-day washout period between each session. The entire trial will be completed in 5 days. Patient prognostic data will be gathered at 3, 6, and 12 months after the conclusion of the study. Figure 1 provides a detailed illustration of the study flow.

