### Behavioral assessments

2.8

The level of consciousness of DoC patients will be evaluated using the CRS-R, which consists of six subscales with a total of 23 items (35). The patients’ consciousness level will be evaluated across six dimensions: auditory, visual, motor, oromotor/verbal, communication and arousal. Comparing the total score, the best score of each subscale can more accurately reflect the patient’s condition. Due to the fluctuating consciousness levels in these patients, we will select the best of five assessments over a 10-day period to represent the patient’s baseline consciousness level. In each session, considering the limited duration of post-effects induced by transcranial stimulation, CRS-R evaluations will be conducted before and after stimulation, focusing on specific items, including the best items from each subscale at baseline and those that are one level above or below the best items. The scores of these specific items will be used to assess whether each session had a behavioral impact on the patient’s consciousness. Patients will undergo reassessment using CRS-R at 3, 6, and 12 months after the conclusion of the trial to collect prognostic data.

It’s worth noting that, in addition to DoC, there are various conditions associated with impaired levels of consciousness. The clinical symptoms of these conditions are summarized in Table 2.

**Table 2 tab2:** Symptoms associated with consciousness states.

State	Consciousness level	Clinical features and manifestations
Alertness/Wakefulness	Full	Full environmental attention; Normal conversation and behavior; Intact orientation; Appropriate responses to all stimuli
Somnolence	Mild impairment	Decreased attention; Slowed responses; Easily arousable; Normal response to strong stimuli
Lethargy	Moderate impairment	Delayed responses; Slurred speech; Requires repeated stimulation; Limited environmental interaction
Stupor	Severe impairment	Responds only to vigorous stimulation; Unable to maintain wakefulness; Minimal verbal response; Limited to pain responses
Coma	Complete loss	Unarousable; No spontaneous behavior; Only reflexive responses; No sleep–wake cycle
Akinetic Mutism	Partially preserved	Eyes open with preserved wakefulness; No spontaneous speech/movement; Limited environmental response; Preserved arousal mechanisms
Apallic Syndrome	Extremely severe impairment	Decorticate posturing; Preserved sleep–wake cycles; No purposeful behavior; Primitive reflexes only

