Patients will be categorized into subgroups based on consciousness levels and prognosis. For consciousness levels, patients will be classified into the MCS or UWS group based on the best result from five baseline CRS-R assessments, To classify a CRS-R record as reflecting MCS, the participant must achieve at least one of the following criteria: a score of 1 on the communication subscale (intentional but non-functional yes/no communication), a score of 3 or higher on the auditory subscale (command-following), a score of 2 or higher on the visual subscale (visual fixation or better), a score of 3 or higher on the motor subscale (localization to noxious stimulation or better), or a score of 3 on the oromotor/verbal subscale (intelligible verbalization). If none of these criteria are met, the CRS-R record will be classified as reflecting UWS (37). For prognosis, patients will be evaluated at 3, 6, and 12 months, with those showing an increase of over 11 Rasch units (approximately 4–6 CRS-R points) (38) classified as the good prognosis group, while others will be placed in the poor prognosis group. A preserved homeostatic plasticity response is defined as a significant modulation of MEP amplitude following the priming-test protocol, consistent with the sliding threshold theory of synaptic plasticity. Its preservation was further compared between the MCS and UWS groups, as well as between the good and poor prognosis groups.

In this study, statistical analysis will be conducted using IBM SPSS Statistics 26 software. The collected data will first undergo normal distribution testing via Kolmogorov–Smirnov tests. If the data meets the criteria for a normal distribution, a three-way repeated measures ANOVA will then be carried out. However, if the data does not adhere to a normal distribution, Friedman’s ANOVA will be utilized instead. Following a significant outcome from the ANOVA, two-way ANOVAs will be conducted within each group to explore temporal changes in mean MEP amplitude. Additionally, Pearson correlation will be used to examine the relationship between homeostatic plasticity retention, consciousness, and prognosis. A significance level of *p* < 0.05 will be employed for determining statistical significance.

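### With open-ended entry after day 28, the unadjusted plasticity–prognosis analysis cannot separate plasticity from time since injury

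*Protocol article*

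**What the plan says.** - **Entry.** Table 1 (section 2.2) requires "Disease onset more than 28 day", and section 2.4 adds "The study process will begin as early as 28 days after the" injury. Both are lower limits. No upper limit on time since onset is stated.
- **Follow-up.** Section 2.4: "Patient prognostic data will be gathered at 3, 6, and 12 months after the conclusion of the study". Section 2.8 uses the same visits and the same starting point. I read both as counted from the patient's own last session.
- **Outcome.** Section 2.11 classes patients as good prognosis by one rule, "with those showing an increase of over 11 Rasch units", whatever the time since injury.
- **Analysis.** Section 2.11: "Pearson correlation will be used to examine the relationship between homeostatic plasticity retention, consciousness, and prognosis". It also plans a group comparison: "Its preservation was further compared between the MCS and UWS groups, as well as between the good and poor prognosis groups". Neither analysis names time since injury as a covariate or stratum.
- **Hypothesis served.** The second of the two in the Introduction: "patients who retain homeostatic plasticity may have a more favorable prognosis".

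**The concern.** Two patients with the same follow-up visit and the same gain threshold may be at very different stages after injury. One may still be in the phase when spontaneous recovery is common; the other may be long past it. If the plasticity index also differs between early and late patients, time since injury is a common cause of both variables in the correlation.

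The effect can go either way. If early patients show more plasticity and recover more, the crude link is larger than the link among patients at a similar stage. If plasticity is low early and returns later, a genuine link is partly cancelled.

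The second hypothesis is at stake. The Discussion goes further and suggests that impaired plasticity might mark an irreversible condition. That reading needs plasticity to carry information beyond how long ago the injury occurred.

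**Working it through.** **Inputs from the article:** 30 patients (15 MCS, 15 UWS); 24 remain after the 20% data loss allowed for in section 2.3 (30 × 0.8 = 24); two-sided 5% level; Pearson correlation. **Inputs not in the article, so assumed:** the mix of early and late patients, their recovery rates, and how plasticity varies with time since injury. The article gives no figure for this association, so there is none to reproduce.

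**1. Stage at follow-up.** Months since injury = months at entry + 3, 6 or 12, ignoring the days spent in the study.

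| Entry (illustrative) | First visit | Second visit | Third visit |
|---|---|---|---|
| 1 month | 4 | 7 | 13 |
| 12 months | 15 | 18 | 24 |
| 24 months | 27 | 30 | 36 |

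**2. Crude link with none inside strata.** Suppose half the patients are early and half late. The index has SD 1 within strata and mean gap d. Good prognosis has probability p₁ early and p₂ late, independent of the index within each stratum. With p̄ = (p₁ + p₂)/2, the crude correlation is

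r = [d(p₁ − p₂)/4] / √[(1 + d²/4) · p̄(1 − p̄)].

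For 60% vs 10% and d = 0.5: 0.0625 / √(1.0625 × 0.2275) = 0.0625 / 0.4917 = 0.13. For d = 0.8 and 1.2, r is 0.19 and 0.27.

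Share of simulated trials with Pearson p < 0.05, n = 30:

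| Good prognosis, early vs late | d = 0.5 | d = 0.8 | d = 1.2 |
|---|---|---|---|
| 40% vs 20% | 6% | 7–8% | 9% |
| 50% vs 20% | 7% | 10% | 14% |
| 60% vs 10% | 10–11% | 18% | 32% |

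Ranges show variation between independent runs. Adjusting for stratum gives about 5% in every cell. With d = 0 the crude test also holds about 5%. At n = 24, 60% vs 10% gives about 9%, 15–16% and 26–27%.

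**3. Continuous version.** Let T be standardised time since injury. With no direct link, the crude correlation is r(T, index) × r(T, recovery).

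| Correlation of T with each | Implied r | Crude rejection, n = 30 | Crude rejection, n = 24 |
|---|---|---|---|
| −0.3 | 0.09 | 7.6% | 7.0% |
| −0.5 | 0.25 | 26.5% | 22% |
| −0.7 | 0.49 | 80.9% | 71% |

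The partial correlation given T rejects in about 5% throughout. The last row is an extreme case.

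**4. Masking.** Take a direct standardised coefficient of 0.5 for the index and −0.5 for T, with T correlated a with the index. The crude correlation is 0.5 − 0.5a.

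| a | Crude r | Power n = 30, crude / adjusted | Power n = 24, crude / adjusted |
|---|---|---|---|
| +0.3 | 0.35 | 49% / 83% | 40% / 73% |
| +0.5 | 0.25 | 26% / 70% | 22% / 60% |

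At n = 30 the crude test loses 83 − 49 = 34 or 70 − 26 = 44 percentage points.

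**The case against.** **This is detail for the analysis plan.** An article need not list covariates for a secondary association, and onset date is needed for eligibility, so adjustment stays possible. That lowers the weight of the point. But the article names the method, and a two-variable Pearson correlation has no place for a covariate. It also states the entry window and the cut-off.

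**The clock is right.** A reader might infer that follow-up should run from injury. The documents do not support that. Follow-up of a prognostic marker properly starts when the marker is measured, and for a late entrant the injury-based visits could fall before testing. This objection stands in full.

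**The crude link is real.** A reader might take the percentages above as false-positive rates for the second hypothesis. They are not. That hypothesis is worded as an association, and in these scenarios the index does predict recovery across the enrolled patients. What is missing is predictive value independent of time since injury.

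**The mechanism is not documented.** The Discussion says homeostatic plasticity supports spontaneous reorganisation after injury. That makes plasticity a driver of recovery; it does not say that plasticity changes with time since injury. The latter is plausible but remains an assumption.

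**Scope.** A reader might extend the point to the MCS–UWS comparison or the primary outcome. MCS and UWS are classified from baseline CRS-R, so follow-up and the gain cut-off play no part, and the calculations here do not address that comparison. The primary MEP contrast of priming types is within patients over a few days, during which time since injury is essentially constant.

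**Conclusion.** The point holds in a limited form. Open-ended entry, one fixed gain cut-off and an unadjusted analysis together mean that the crude plasticity–prognosis result can be inflated or masked by time since injury. It cannot by itself support a claim that plasticity predicts outcome independently.

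The harm requires time since injury to relate to both recovery and plasticity. The first is likely and the second possible; the documents quantify neither. Mild stratum assumptions move the rejection rate only slightly above 5%, and only a steep recovery contrast with a large index gap takes it to about a third. In the masking direction, the assumed settings cost roughly 34 to 44 points of power at n = 30.

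**What to change.** In section 2.11, keep the crude correlation and add the plasticity–prognosis association adjusted for log time since onset. Use either a partial correlation or a regression of CRS-R gain on the plasticity index. State that any claim of independent prognostic value rests on the adjusted result. Report each follow-up in months since injury as well as months since the sessions, keeping the present starting point.

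The cost is analysis wording and one degree of freedom in 24 to 30 patients. No visit, procedure or sample size changes, and onset date is already needed for eligibility. Adjustment on the log scale assumes a roughly linear relation in log time, which a scatter plot can check. Cause of injury as a second covariate is optional; nothing above depends on it.

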**Figure 1 fig1:**
[figure not shown]
Study flow diagram. HC, health controls; MCS, minimally conscious state; UWS, unresponsive wakefulness syndrome; CRS-R, Coma Recovery Scale-Revised; fMRI, functional magnetic resonance imaging; EEG, electroencephalography; MEP, motor evoked potential; tDCS, transcranial direct current stimulation; iTBS, intermittent theta burst stimulation; A, anodal tDCS; C, cathodal tDCS; S, sham tDCS.

Adverse events will be promptly recorded and reported during the trial. Following this, experts will evaluate the connection between adverse events and the trial based on previous literature reports. If a severe adverse event is determined to be linked to the intervention, the trial will be immediately halted, and necessary medical actions will be taken for the patient until the concern are properly resolved.

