In this study, tDCS and TMS will be used to detect homeostatic plasticity retention in patients with DoC. tDCS applies low-amplitude (1–2 mA) direct current to the brain via two scalp electrodes, modulating the threshold of action potential generation, thereby depolarizing (anode) or hyperpolarizing (cathode) individual neurons (9, 44, 45). TMS is a technique that integrates nerve stimulation and cortical excitability detection. It uses electromagnetic induction to induce secondary currents in subcortical neurons, thereby activating neurons to change physiological processes in the brain (46, 47).

While two NTBS technologies, tDCS and TMS, are widely used in the field of treatment for DoC, the selection of parameter and targets often relies on studies related to other diseases or healthy individuals. In DOC, the most common targets are the M1 or the dorsolateral prefrontal cortex (DLPFC) rather than the anterior cingulate cortex or posterior cingulate gyrus emphasized by many theories of consciousness. M1 is frequently targeted in the motor rehabilitation of stroke patients, while DLPFC is primarily employed in depression treatment (48). Such empirical transplantation carries significant theoretical risks—severe brain injury may fundamentally alter homeostatic plasticity mechanisms, and directly applying neuromodulation parameters from healthy populations may lead to diminished efficacy or even induce secondary damages such as epilepsy.

Based on these findings, we propose a stepwise intervention strategy. The primary task is to assess the retention of homeostatic plasticity in DoC patients. For patients with impaired homeostatic plasticity, priority should be given to restoring this mechanism before proceeding with neuromodulation treatments to prevent uncontrolled risks caused by impaired negative feedback regulation. Previous successes in dopamine modulation for Parkinson’s disease (22) suggest that the neurotransmitter system may serve as an important regulatory target. In some cases, impaired homeostatic plasticity might even indicate the irreversibility of a patient’s condition.

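### Previous literature reports are the only stated basis for relatedness, so a severe event caused by stimulation but with little or no precedent could be judged unlinked and miss the stated halt

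*Protocol article*

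**What the plan says.** The last paragraph of section 2.4 (Procedures) in the protocol article, placed after Figure 1, handles adverse events in three steps.

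1. Capture: "Adverse events will be promptly recorded and reported during the trial".
2. Attribution: "experts will evaluate the connection between adverse events and the trial based on previous literature reports".
3. Action: "If a severe adverse event is determined to be linked to the intervention, the trial will be immediately halted". Medical care for the patient follows until the matter is resolved.

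The Discussion (section 3) bears on the subject from a distance. It says that tDCS and TMS "are widely used in the field of treatment for DoC". It also warns that "severe brain injury may fundamentally alter homeostatic plasticity mechanisms" and that "directly applying neuromodulation parameters from healthy populations may lead to diminished efficacy or even induce secondary damages such as epilepsy". For patients with impaired homeostatic plasticity it advises restoring that mechanism before treatment, "to prevent uncontrolled risks caused by impaired negative feedback regulation".

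**The concern.** Two questions are asked of any adverse event. Is it already known for this kind of intervention, that is, expected? And did the intervention cause it in this person? The second also needs the timing relative to stimulation, the clinical course and the competing explanations. In severely brain-injured patients there are usually several competing explanations. The article directs the experts to the kind of evidence that mainly answers the first question, and then lets the result govern a safety action that should rest on the second.

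At stake is the halt. If a severe event has no counterpart in earlier reports, or is unusual in severity or timing, an expert who follows the sentence as written has little ground for calling it linked, and the halt does not apply. Most participants are patients who cannot consent for themselves and are enrolled through a legal representative, so the rule that protects them should be worded with care.

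**Working it through.** No arithmetic applies. The point does not depend on sample size, power, alpha or an event count. The check is a reading of the text.

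**Step 1: is there another stated basis for relatedness?** The rest of the article was read for one. Timing after stimulation, clinical course, alternative causes and recurrence across a participant's three sessions are not mentioned in connection with adverse events. Literature reports are the only basis stated.

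**Step 2: is there a halt that does not need the link?** None is stated. The single halt in section 2.4 requires that the severe event be determined to be linked. The scope of the halt is open, because the same section says "The entire trial will be completed in 5 days", where trial means one participant's course. The halt may thus stop one participant or the whole study. The link is required under either reading.

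**Step 3: what happens to a severe event if precedent alone decides?**

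| | Well documented in earlier reports | Little or no precedent |
|---|---|---|
| Caused by stimulation | Judged linked; halt applies | May be judged unlinked; halt may not apply |
| Not caused by stimulation | May be judged linked; at worst a needless halt | Judged unlinked; correct |

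Only the upper right cell is a safety gap. The Discussion itself names epilepsy as a possible harm, so a seizure falls in the left column and would very likely be linked.

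**Step 4: does the article suggest that the upper right cell could be occupied?** Only indirectly. The Introduction's first hypothesis is that these patients have impaired homeostatic plasticity, and the Discussion attaches uncontrolled risks to that impairment. It also doubts that experience from healthy people carries over to severe brain injury. The remark about wide use in DoC refers to tDCS and TMS as technologies and does not say whether it covers the two given in sequence, as here. These statements give a reason not to rest on earlier reports alone. They are about choosing parameters and preparing patients for treatment, not about attributing events, and they identify no unprecedented harm.

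**Step 5: what still works if attribution fails?** Under section 2.4 the event has been recorded and reported before attribution, and the representative may withdraw the patient at any time without giving a reason. The weakness lies in the attribution step and not in event capture.

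**The case against.** The strongest reply is that a journal article condenses the full protocol. Three sentences on adverse events cannot carry a causality scale, and naming one input does not show that the full procedure excludes the others. The sentence does not say that literature is the only basis. It has experts judge the connection, which is a relatedness judgement, and earlier reports are a legitimate part of it. The halt sentence does not repeat the literature basis. The residual case needs an event that is severe, truly caused by stimulation, without precedent and also misjudged by experts. Active seizures and unstable vital signs are exclusions in Table 1, which lowers the risk at entry.

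Much of this stands. A reader might infer that the rule tests expectedness instead of causality, or that experts are barred from clinical judgement. The text supports neither. A reader might also take the Discussion's warnings as proof that the literature is unsuitable for attribution. They do not show that: they concern treatment parameters, and section 2.4 does not restrict the reports to healthy populations.

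The condensation argument does not dispose of the point. The article does not leave the criterion to another document; it states one, and that one governs the only halt. Relying on experts to go beyond the written rule is no answer when the rule can be corrected in a sentence.

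**Conclusion.** The point holds in a limited form. The only stated basis for relatedness is one that, used alone, can miss a severe event caused by stimulation with little or no precedent, and the only stated halt depends on that judgement. It does not follow that known harms would be missed, that events would go unrecorded, or that the safety rule fails in general.

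The conclusion assumes that the sentence is applied as written and that no fuller causality procedure exists in a document not shown. If such a procedure exists, the article's sentence should simply be brought into line with it.

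The size cannot be quantified, because the document gives nothing from which a rate of misattribution or harm could be derived. A reader might be tempted to count the sessions that could still be given after a missed halt. That count would be the same for any missed halt, whatever its cause, and it measures exposure and not harm, so it says nothing about the size of this weakness. The primary outcome, the randomisation and the analysis are unaffected. The change is worth making because it is nearly free and concerns participant safety.

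**What to change.** Replace the attribution sentence in section 2.4, for example with: *Experts will judge the relatedness of each adverse event case by case, on its timing relative to stimulation, the clinical course and alternative causes, with published reports as one input; absence of prior reports will not count against relatedness.*

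The halt sentence can stay as it is for this purpose. The cost is the rewording of one sentence. The small downside is that more events may be classed as possibly related, with the review effort that this brings.
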